# Development and evaluation of a patient centered cardiovascular health education program for insured patients in rural Nigeria (QUICK - II)

**DOI:** 10.1186/1471-2458-11-171

**Published:** 2011-03-21

## Abstract

**Background:**

In Sub Saharan Africa, the incidence of hypertension and other modifiable cardiovascular risk factors is growing rapidly. Poor adherence to prescribed prevention and treatment regimens by patients can compromise treatment outcomes. Patient-centered cardiovascular health education is likely to improve shortcomings in adherence. This paper describes a study that aims to develop a cardiovascular health education program for patients participating in a subsidized insurance plan in Nigeria and to evaluate the applicability and effectiveness in patients at increased risk for cardiovascular disease.

**Methods/Design:**

*Design: *The study has two parts. Part *1 *will develop a cardiovascular health education program, using qualitative interviews with stakeholders. Part *2 *will evaluate the effectiveness of the program in patients, using a prospective (pre-post) observational design.

*Setting: *A rural primary health center in Kwara State, Nigeria.

*Population: *For part 1: 40 patients, 10 healthcare professionals, and 5 insurance managers. For part 2: 150 patients with uncontrolled hypertension or other cardiovascular risk factors after one year of treatment.

*Intervention: *Part *2*: patient-centered cardiovascular health education program.

*Measurements: *Part 1: Semi-structured interviews to identify stakeholder perspectives. Part 2: Pre- and post-intervention assessments including patients' demographic and socioeconomic data, blood pressure, body mass index and self-reporting measures on medication adherence and perception of care. Feasibility of the intervention will be measured using process data.

*Outcomes: *For program development (part 1): overview of healthcare professionals' perceptions on barriers and facilitators to care, protocol for patient education, and protocol implementation plan.

For program evaluation (part 2): changes in patients' scores on adherence to medication and life style changes, blood pressure, and other physiological and self-reporting measures at six months past baseline.

*Analysis: *Part 1: content analytic technique utilizing MAXQDA software. Part 2: univariate and multilevel analysis to assess outcomes of intervention.

**Discussion:**

Diligent implementation of patient-centered education should enhance adherence to cardiovascular disease prevention and management programs in low income countries.

**Trial Registration:**

ISRCTN47894401

## Background

Sub Saharan African (SSA) countries are currently experiencing a rapid increase in the incidence of cardiovascular diseases (CVD) [1,2]. Hypertension is an important risk factor for CVD. Poor adherence to prescribed medication regimens or lifestyle advices can severely compromise the effectiveness of CVD prevention and treatment [3]. For that reason, the World Health Organization (WHO) emphasizes in a recent report that any attempt to improve cardiovascular care should also address the issue on non-adherence [3]. The views and beliefs of patients regarding disease conditions and treatment may differ from medical perceptions, and it is well documented that patients do have significant roles to play in adherence to medications and lifestyle measures [4-6]. Evidence to date indicates that patient education is one of the most successful interventions to improve adherence and patient self-management of chronic diseases, especially if the education addresses patients' beliefs and concerns about the condition and treatment, identifies social cultural and individual barriers to adherence and enhances patients' confidence in their ability to overcome those barriers [7].

In this paper, we describe the design of a study that has the aim to develop and test a program for cardiovascular health education for patients who are enrolled in a subsidized, community-based health insurance program in Nigeria and are at an increased risk of developing CVD. This study is part of the project "QUality Improvement for Cardiovascular care Kwara (QUICK)". The project will be evaluated by two studies: QUICK-I and QUICK-II. This paper describes the design of the QUICK-II study that focuses on patient education. A detailed description of the insurance program and the QUICK-I study can be found elsewhere [8].

### Aim of the study

The World Health Organization/International Society of Hypertension (WHO/ISH) guidelines recommend patient education as part of CVD prevention care [9], but they do not provide clear recommendations on how this education should be delivered and tailored to the specific target groups in the region. We hypothesize that tailored patient education will improve adherence to cardiovascular care among patients.

For that reason, the main aims of QUality Improvement Cardiovascular care Kwara II (QUICK - II) are:

1. To develop and implement a targeted cardiovascular health education program (CHEP) for patients participating in the Hygeia Community Health Plan (HCHP)

2. To evaluate the newly developed program with respect to its applicability and effectiveness in patients at an increased risk for CVD

## Methods

### Project design

#### QUICK - II consist of two consecutive parts

In *part 1 *of the study, we will develop a stakeholder based Cardiovascular Health Education Program (CHEP) that is to be used to educate patients at risk of CVD who are enrolled in a private health insurance plan in rural Nigeria. To develop CHEP, we will use the following step-wise approach: (i) open qualitative interviews will be conducted with key stakeholders in CVD care to explore their perceptions on CVD, CVD risk factor management and CVD prevention and care. These stakeholders include patients at risks for CVD, healthcare providers (HCP), and health insurance managers of HCHP; (ii) on the basis of the outcomes of interviews with patients, CHEP will be developed; (iii) supportive strategies needed to implement CHEP successfully will be identified on the basis of the outcomes of the interviews with HCP and health insurance managers.

In *Part 2 *of the study we aim to evaluate the effect of CHEP through a prospective hospital-based study, using a pre-post intervention design. Measurements will be conducted in a subset of patients included in QUICK - I: those who have uncontrolled hypertension or other CVD risk factors, or are non adherent to medication after 12 months of treatment.

In addition, case file data will be reviewed and interviews with health care professionals in the participating clinic will be held and analyzed to evaluate the feasibility of the application of CHEP in practice.

### Setting

Ogo Oluwa Hospital (OOH) in Bacita (Kwara State). A detailed description of this setting can be found in the accompanying paper describing the QUICK-I study design [8].

Because part 1 and part 2 of this study have different designs, we will describe the study procedures in different sections.

## Part 1: Development of Chep

### Study Population

The study population for Part 1 will consist of four groups: *Group 1 *- A purposeful sample of 20 patients with 'controlled hypertension' equally distributed by gender (50% male and female), and age (18-35 yrs, 36-55 yrs, 56 yrs and over) who were included in the QUICK - I study; *Group 2 *- A purposeful sample of 20 patients with 'uncontrolled hypertension' equally distributed by gender (50% male and female), and age (18-35 yrs, 36-55 yrs, 56 yrs and over) who were included in QUICK - I study; *Group 3 *- Eight to ten healthcare professionals treating patients with hypertension (HTN), diabetes mellitus (DM) or CVD at OOH; and *Group 4 *- Five to ten managers and doctors of the Health Maintenance Organization (HMO) Hygeia.

### Sample size and Recruitment

#### Sample size

For qualitative interviews, data saturation is a criterion for calculation of the sample size. In general, about 20 interviews are required until saturation is reached and no new information on the major themes is collected [10,11]. For that reason we decided to interview 40 patients (20 with controlled and 20 with uncontrolled hypertension). The number of interviews for HCP is less because the number of health care professionals working in the region is limited. The same accounts for health insurance managers and doctors of Hygeia HMO.

#### Patient recruitment

The patients in Groups 1 and 2 will be recruited among participants in the QUICK - I study in the first month after their inclusion. Health care professionals (Group 3); and managers and doctors working for Hygeia HMO (Group 4) will be included in the first 3 months of QUICK - I. Eligible respondents will be adequately informed of the objectives of the qualitative study. Permission for the interview and written or tape-recorded informed consents will be taken.

### Outcomes

The outcomes envisaged for part 1 include: (i) an overview of patients' perceptions on CVD, CVD risk factors and inhibiting or facilitating factors for CVD prevention and care; (ii) an overview of perceptions of HCP, and health insurance managers and doctors of Hygeia HMO on barriers and facilitators to implementation of CVD prevention and care; (iii) a protocol for CHEP; and (iv) a plan of supportive strategies for implementation of CHEP, including training for HCP.

### Materials and measurements

In part one, patients allocated to Groups 1 and 2 will be interviewed using a semi-structured questionnaire that is based on a topic list used in a similar study by Beune et al [12], but modified to suit the Nigerian setting. Healthcare professionals from Groups 3 and 4 will similarly be interviewed using semi structured questionnaires based on topic lists specifically designed to address the particular concerns of these groups. A researcher who speaks English and Yoruba fluently, assisted by interpreters in Nupe, the other dominant local language, will conduct interviews. CHEP will be developed based on a systematic review of literature on similar past patient education programs, and analysis of the interview data.

### Data management and analysis

#### Data entry and cleaning

The researcher will transcribe the semi-structured interviews conducted in part 1 and check unclear passages with respondents, if needed.

#### Data analysis

The transcribed qualitative interview data will be analyzed using content analytical techniques: fragments containing the respondents' ideas about major themes, for example inhibitors or facilitators of cardiovascular diseases care, will be identified from each interview and coded. Similar codes will be assigned to related statements, resulting in a code list for each interview. Code lists will be compared to identify common and unique themes, leading to a thematic matrix for each group of respondents. Similarities, variations and patterns between groups will be compared, using these matrices.

Data entry and analysis will be supported by MAXQDA software http://www.maxqda.com. MAXQDA facilitates data management, the assignment of labels, codes and themes to text fragments and the generation of thematic matrices containing these elements. In the past, MAXQDA software has been successfully used in similar studies [13].

## Part 2: Evaluation of Chep

### Study population

To be included in the evaluation study of the effect of CHEP (part 2), patients have to meet the following inclusion criteria. They must: (i) be enrolled in HCHP; (ii) be registered as a patient in OOH; (iii) be included in the QUICK - I study for at least 12 months; (iv) have a diagnosis of hypertension; (v) have uncontrolled BP (≥140 mmHg systolic or ≥90 mmHg diastolic) or be non adherent to prescribed medication or any other recommended life style changes according to their score on the Morisky scale [14]; and (vi) be ≥18 years of age. Patients who meet these inclusion criteria will be excluded if their treating health care professional judges them unfit for participation (e.g. due to co morbidity) or if they are not capable or unwilling to give informed consent. Female patients who are pregnant or lactating will be excluded from the entire study because the etiology, prognosis and treatment regimes of gestational diabetes and pregnancy-induced hypertension are different compared to hypertension and diabetes in non-pregnant women.

To be included in the qualitative interviews for the feasibility analysis, healthcare professionals must: (i) be a HCP in OOH who participated in the implementation of CHEP, or be managers and doctors of HCHP; and (ii) give informed consent.

Table 1 shows an overview of the inclusion and exclusion criteria for CHEP study. For an overview of the inclusion and exclusion criteria of QUICK - I, see the article of the QUICK - I study design [8].

**Table 1 T1:** Inclusion and exclusion criteria for CHEP study.

Inclusion Criteria	Exclusion Criteria
Patients:	Patients:
• Enrollment in HCHP	• Unwillingness to give informed consent
• Registered and accessing care in OOH	• Unfit for participation (e.g. due to co morbidity)
• Inclusion in QUICK - I for at least 12 months	• Pregnant or lactating females
• Diagnosis of hypertension	
• Uncontrolled hypertension or non adherence to prescribed medication or lifestyle changes after 12 months in QUICK - I	
• Age of 18 years and over	
• Give informed consent	

Healthcare Professionals for interviews on feasibility of CHEP:	
• HCP of OOH who participated in the implementation of CHEP, or	
• Managers and Doctors of HCHP	
• Give informed consent	

Figure 1 describes the project populations for QUICK - II and their relationship to the QUICK - I study.

**Figure 1 F1:**
[figure not shown]
**Project populations and relationship between QUICK - I and CHEP study in QUICK - II**.

### Outcomes

The primary outcome of the evaluation of CHEP will be the changes in adherence to medication or life style recommendations. This will be assessed through the Morisky self-report medication adherence questionnaire [14]. This scale asks patients to respond yes or no to five questions. Each positive answer is assigned a score of one, with higher scores indicating poorer adherence. The same scale will be used for other life style recommendations (e.g. salt intake). As such, self-reported adherence will be assessed as a continuous measure.

Secondary outcomes are changes in physiological measures - systolic blood pressure, diastolic blood pressure, and body mass index (BMI) or abdominal obesity at 6 months after baseline.

Table 2 indicates definitions of what we consider as significant improvement per outcome measure.

**Table 2 T2:** Definitions of significant improvement per outcome measure

Outcomes	Significant improvement
Adherence to medication and life style recommendations (Primary outcomes)	Using the distribution on the Morisky scale [14] of low, medium, and high adherence ratios, a post CHEP effect shift of 10% to a higher category will be defined as a significant improvement in adherence.

Blood pressure (Secondary outcome)	Blood pressure decrease of >10% systolic or diastolic or blood pressure at target level (patients without diabetes or established CVD: <140 mmHg systolic and <90 mmHg diastolic, patients with diabetes, renal disease or established CVD: <130 mm Hg systolic and <80 mmHg diastolic).

Body mass index (kg/m^2 ^)	No CVD risk: <25 Moderate CVD risk: 25-30 High CVD risk: >30 In patients with a BMI >25 any reduction of BMI at 6 months will be regarded as an improvement.

Data will also be collected about other factors that may influence patients' hypertension management: self-reported cardiovascular risk factors (physical activity, diet, smoking, alcohol, sodium intake), knowledge of HTN and HTN management, perceptions of HTN, perceptions of medications, self efficacy, experienced stress, patient satisfaction with care (e.g. doctors' performance, supply of medication, frequency of follow up, satisfaction with CHEP etc).

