### Sample size and Recruitment

#### Sample size calculation

The power analysis for sample size is based on the difference between the adherence score after implementation of CHEP and the adherence score at baseline using the 5-item Morisky adherence scale. Using the Morisky distribution of low, medium, and high adherence ratios of 32%, 52% and 16% respectively [14], and an estimated post CHEP effect shift of 10% to a higher category, we will need a minimum sample size of 150 patients.

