### Data Analysis

#### Statistical methods

The rate of adherence will be examined according to the intention to treat principle. Primary and secondary outcome measures will be calculated for every patient at baseline and 6 months thereafter to assess possible improvements. Furthermore, univariate and multi-level analyses will be performed to evaluate the modifying effect of the outcome measures (see above) on adherence or blood pressure. If the N is sufficient, we will perform separate subgroup analyses for gender. While a *p *value of 0.05 will be the critical value for all analysis, the *p *value will be adjusted for subgroup analysis according to standard procedures.

Data from interviews with HCP will be analyzed and used to identify potential barriers to the implementation of CHEP in practice.

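### The primary adherence outcome is worded two ways with no success rule, and 0.05 is adjusted only for subgroups: if either outcome suffices, family-wise error can reach 9.75%

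*Protocol article*

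**What the plan says.** The protocol article describes the primary outcome of the evaluation in several places, and they do not agree.

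- Part 2, Outcomes, uses the singular and *or*: "The primary outcome of the evaluation of CHEP will be the changes in adherence to medication or life style recommendations".
- Table 2, in the same section, uses *and* and the plural: "Adherence to medication and life style recommendations (Primary outcomes".
- The lifestyle component is scored by reusing the medication instrument: "The same scale will be used for other life style recommendations (e.g. salt intake". Table 3 lists medication adherence and lifestyle adherence on separate rows. No combined score is defined.
- Table 2 gives one improvement criterion for the pair: "a post CHEP effect shift of 10% to a higher category will be defined as a significant improvement in adherence". It does not say whether one or both outcomes must shift.
- Statistical methods makes a p "value of 0.05 will be the critical value for all analysis" and adds that the p "value will be adjusted for subgroup analysis according to standard procedures". No other adjustment is mentioned.
- Sample size calculation is "based on the difference between the adherence score after implementation of CHEP and the adherence score at baseline using the 5-item Morisky adherence scale". It uses one category distribution (32%, 52%, 16%) and arrives at 150 patients.

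**The concern.** A reader cannot tell from the article which result would make the programme a success on its primary outcome. Two adherence measures are called primary and each could be tested at 0.05. The only multiplicity rule in the text covers subgroups and leaves these two out.

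This goes beyond detail that a condensed article leaves to an analysis plan. The identity of the primary outcome is a protocol matter, and here two statements about it in one section differ. The significance rule is also stated, and stated with a limited scope.

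Two things are at stake. If improvement on either measure counts, the chance of a false primary success exceeds 5%, and the claim can rest on whichever measure moved. If both must improve, a sample size built on one score does not show the power of the joint requirement. The study is an uncontrolled pre-post comparison with self-reported primary measures, so room to choose the outcome after seeing results is best removed beforehand.

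**Working it through.** **1. The plan's own figure, N = 150**

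Inputs from Sample size calculation: baseline low/medium/high 32%/52%/16% and a 10% shift to a higher category. Power, sidedness and the pre-post correlation are not stated, so 150 cannot be reproduced uniquely.

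One reading moves 10 percentage points from low to medium and 10 from medium to high, giving 22%/52%/26%. Score the categories 0, 1, 2:

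- Baseline mean 0.52 + 2 × 0.16 = 0.84; follow-up mean 0.52 + 2 × 0.26 = 1.04; difference 0.20.
- Baseline variance 0.52 + 4 × 0.16 − 0.84² = 0.4544; follow-up variance 0.52 + 4 × 0.26 − 1.04² = 0.4784.
- N = (z for alpha + z for power)² × (0.4544 + 0.4784 − 2ρ√(0.4544 × 0.4784)) / 0.20².

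With two-sided 0.05 and ρ = 0 this gives 184 (80% power) or 246 (90%). It gives 150 at ρ near 0.18 (80%) or near 0.39 (90%). So 150 is compatible with one test at two-sided 0.05 under assumed correlations. The calculation describes a single outcome, with no alpha split and no joint requirement.

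**2. If either outcome suffices**

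Two tests, each two-sided 0.05 (sidedness assumed). For independent tests:

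family-wise error = 1 − 0.95² = 0.0975.

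For test statistics with correlation r, the error is 1 − P(|Z1| < 1.96 and |Z2| < 1.96) under a bivariate normal distribution. The documents give no r, so a range is shown:

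| Assumed r | Family-wise error | Ratio to 0.05 |
|---|---|---|
| 0 | 0.0975 | 1.95 |
| 0.3 | 0.0951 | 1.90 |
| 0.5 | 0.0907 | 1.81 |
| 0.7 | 0.0835 | 1.67 |
| 0.9 | 0.0704 | 1.41 |
| 1 | 0.0500 | 1.00 |

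**3. If both must succeed**

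The false-success probability cannot exceed that of either test alone, so it is at most 0.05. The cost is in power. If each outcome had 80% power (assumed), joint power would be 0.80 × 0.80 = 64% for independent tests, rising to 80% only at perfect correlation.

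**4. What an alpha split would do**

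At 0.025 each, the family-wise error is 1 − 0.975² = 0.0494 for independent tests, and less with positive correlation. To keep the same power for each outcome at 0.025:

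- 80% power: 150 × (2.241 + 0.842)² / (1.960 + 0.842)² ≈ 182.
- 90% power: 150 × (2.241 + 1.282)² / (1.960 + 1.282)² ≈ 178.

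**The case against.** The strongest objection is that the article contains no rule that one success is enough. The *or* in the Outcomes text may only describe what is measured. Table 2, the Abstract and Materials and Measurements all use *and*; if that means both must improve, there is no inflation. A single combined adherence result is also conceivable. This stands, and it is why the error figures above are conditional.

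A reader might infer that the chance of a false primary success simply is about double the stated level. The document does not support that. It needs the unstated either-one rule, and 9.75% is the figure for independent tests. Both measures use the same self-report scale in the same patients at the same visits, so positive correlation is likely and the error would be lower.

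A reader might also infer a larger inflation from testing several lifestyle recommendations separately. Salt intake is given only as an example and the number of lifestyle tests is not stated, so no figure can be put on this.

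Table 2 also defines improvement as a category shift rather than a p value, so 9.75% is not the probability of meeting that criterion. It applies to tests at the 0.05 level that Statistical methods sets for all analyses.

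Finally, it would go too far to say that the lifestyle outcome has no power basis. The sample size text speaks of an adherence score without confining it to medication, and the same scale serves both. What is missing is a calculation for two outcomes considered together.

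**Conclusion.** The point holds as an unresolved primary outcome and success rule. The Outcomes text and Table 2 disagree, and the stated multiplicity rule leaves out the two outcomes labelled primary. As written, the plan permits two unadjusted primary tests without saying which carries the claim.

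The size is conditional. Under an either-one rule with two two-sided tests at 0.05, the family-wise error is at most 9.75%, and about 8.3% to 9.5% for assumed correlations of 0.7 to 0.3. Under a both-required rule there is no inflation, but joint power at N = 150 is not given. Each reading leaves something to settle, so the correction should be made before the data are analysed.

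**What to change.** Make the Outcomes text and Table 2 agree, and add the success rule to Statistical methods. Any one of these is sufficient:

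- **One primary outcome, fixed sequence.** Name one adherence measure as primary and test the other at 0.05 only if the first is significant. Medication adherence fits the questionnaire cited, but nothing in the document ranks it above lifestyle adherence, so the choice is the sponsor's. The primary loses no alpha. Success on the second outcome alone can no longer be claimed as primary.
- **Both primary, Holm at an overall 0.05.** The smaller p value must meet 0.025; the other is then tested at 0.05. Either outcome can support a primary claim. The price is some power at N = 150, or about 178 to 182 patients if each outcome is to keep its power at 0.025 (90% or 80% assumed).
- **Both required.** State this, keep 0.05 for each, and report the joint power of 150 patients under a stated correlation.

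If one combined score was intended, define it in Outcomes and use it in Table 2 and in the sample size text. The change takes one sentence in Outcomes and one in Statistical methods, with the Table 2 label aligned; data collection is unaffected.

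### Table 2's 10% threshold for a significant improvement in adherence leaves gross or net shift undefined, equals the planning effect, and can contradict the 0.05 criterion

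*Protocol article*

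**What the plan says.** The protocol article fixes the assessment of the primary outcome in four places.

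- **Outcomes, text.** Adherence is scored on five yes/no Morisky items, higher being worse: "As such, self-reported adherence will be assessed as a continuous measure".
- **Outcomes, Table 2.** The same outcome is judged on three categories (low, medium, high), and "a post CHEP effect shift of 10% to a higher category will be defined as a significant improvement in adherence".
- **Sample size calculation.** The inputs are given as "Using the Morisky distribution of low, medium, and high adherence ratios of 32%, 52% and 16% respectively", together with "an estimated post CHEP effect shift of 10% to a higher category", leading to "we will need a minimum sample size of 150 patients".
- **Statistical methods.** A p "value of 0.05 will be the critical value for all analysis".

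Part 2 has no control group; the abstract describes it as "using a prospective (pre-post) observational design". Nothing says whether Table 2 or the 0.05 criterion decides whether adherence improved.

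**The concern.** Table 2 is the article's only explicit definition of success on the primary outcome, and it is a bare threshold on an observed proportion. Three things follow.

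1. The rule is not unique. It can be read as gross (all who move up) or net (up minus down), and as points or relative.
2. The threshold is the planning effect itself, so an observed net shift has to reach its own expected value.
3. The rule takes no account of sampling error and the 0.05 criterion does, so the same data can yield a significant improvement under one and not under the other.

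At stake is the headline conclusion of Part 2. With no ranking between the criteria, the choice could be made after the data are seen.

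**Working it through.** **Inputs from the article.** N=150; categories 32/52/16%; shift 10%; critical p 0.05. Not given: power, test, sidedness, within-patient correlation, and test-retest reliability of the scale.

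**Step 1. The plan's own figure.** N=150 cannot be reproduced uniquely. With u the share moving up and d the share moving down, the McNemar formula is

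n = [z_α√(u+d) + z_β√((u+d) − (u−d)²)]² / (u−d)².

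- u=17%, d=7%, one-sided 0.05, 80% power: (1.645·√0.24 + 0.842·√0.23)²/0.01 = 146.3, so 147.
- u=14%, d=4%, one-sided 0.05, 90% power: (1.645·√0.18 + 1.282·√0.17)²/0.01 = 150.4, so 151.

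Both come close to 150, but each needs inputs that the article does not state. The figure is neither confirmed nor shown wrong.

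**Step 2. What 10% could mean.**

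- Ten percentage points of all patients: 0.10 × 150 = 15 patients.
- Ten per cent of those who can move up: 0.10 × (32% + 52%) = 8.4%, or 12.6 patients.
- Ten points across each of the two category boundaries: 20%, or 30 patients.

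The first meaning is used below.

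**Step 3. Net reading, planned effect true.** Let U and D be the numbers moving up and down, multinomial with u = d + 0.10:

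P(U−D ≥ 15) = Σ_k Bin(k; 150, d) · P[Bin(150−k, u/(1−d)) ≥ k+15].

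| Downward rate d | P(net ≥10%) | P(net >10%) |
|---|---|---|
| 0 | 0.54 | 0.43 |
| 5% | 0.53 | 0.46 |
| 10% | 0.53 | 0.47 |
| 20% | 0.52 | 0.48 |

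A larger N does not cure this, because the threshold sits at the centre of the sampling distribution.

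**Step 4. Net reading, no effect (u = d).** P(U−D ≥ 15) = 0.0001, 0.004, 0.015 and 0.031 for up-move rates of 5, 10, 15 and 20%.

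**Step 5. Gross reading, no effect.** P(U ≥ 15) with U ~ Bin(150, u). To obtain u, assume two bivariate-normal latent scores with correlation r, both cut at the 32% and 84% points, so that the margins are 32/52/16 on each occasion. The values of r are assumptions.

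| r | Up-moves by chance | P(≥15 of 150) |
|---|---|---|
| 0.7 | 18% | 0.998 |
| 0.8 | 15% | 0.98 |
| 0.9 | 11% | 0.66 |
| 0.95 | 7.6% | 0.17 |
| 0.98 | 4.8% | 0.006 |

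**Step 6. Table 2 against p<0.05.** Exact two-sided sign test on the movers, N=150.

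| Up / down | Gross | Net | Table 2 | p |
|---|---|---|---|---|
| 45 / 30 | 30% | 15/150 = 10% | met on both readings | 0.105 |
| 13 / 2 | 13/150 = 8.7% | 11/150 = 7.3% | met on neither | 0.007 |
| 15 / 15 | 10% | 0% | met if gross only | 1.0 |

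**Step 7. Power of a 0.05 test, for contrast.** The normal approximation for a two-sided McNemar test at a net shift of +10 points is Φ{[0.10·√150 − 1.96·√(u+d)] / √[(u+d) − 0.01]}. It gives about 91, 79, 61 and 41% at downward rates of 2, 5, 10 and 20%. This quantity differs from Step 3 and varies strongly with the amount of two-way movement.

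**The case against.** The strongest reply is that Table 2 was never meant as the trial's test. Its other rows (a blood pressure fall or target, any reduction in a raised BMI) read as definitions of worthwhile change, and the article sets 0.05 separately for all analyses. Any relevance threshold placed at the planning effect is exceeded about half the time when that effect is true. A condensed article may also leave the named test to a fuller document.

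Much of this stands. The absence of a named test is not the finding, and two stronger inferences should be resisted.

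- **That the study has only 50% power.** Step 3 gives the chance of reaching the Table 2 threshold. The sample size section describes its basis differently: "The power analysis for sample size is based on the difference between the adherence score after implementation of CHEP and the adherence score at baseline". Power of a 0.05 test is a separate matter (Step 7).
- **That chance alone would nearly always produce a declared success.** This needs the gross reading and about 10% or more of patients moving up by chance, which in the model means a correlation of about 0.9 or lower. The article gives no reliability figure. Its wording ties the shift to the distribution over the three categories, which fits a net shift at least as well, and there the chance rate is about 3% or less (Step 4).

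What the reply does not remove is that Table 2 calls its threshold a significant improvement, gives no gross or net definition, and is not ranked against the 0.05 criterion that it can contradict.

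**Conclusion.** The point holds as a defect in a stated rule. Without any assumption about reliability, the Table 2 rule has more than one meaning and conflicts with the 0.05 criterion in realistic data (Step 6). On the net reading in percentage points it is met 52-54% of the time at N=150 when the planned effect is true, or 43-48% if more than 10% is required. The second discordant example depends on reading 10% as a share of all patients: under the 8.4% version, 13 up would pass on a gross count, though still not on a net one.

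The risk that an ineffective programme passes is conditional. It exists on the gross reading only, and runs from 0.006 to 0.998 over assumed correlations from 0.98 down to 0.7. That range rests on the latent-normal model and on the 32/52/16 margins holding for the enrolled patients. The article also judges one primary outcome both as a continuous score and by categories; any repair has to settle that too.

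**What to change.** Replace the primary-outcome cell of Table 2, and add one matching sentence to Statistical methods, along these lines: improvement in adherence is concluded when the paired change in Morisky score from baseline to 6 months differs from zero, in the direction of better adherence, at two-sided 0.05; the mean change is reported with its 95% CI.

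This uses the continuous measure already named under Outcomes and leaves a single criterion. Keep the 10-point category shift, defined as the percentage moving up minus the percentage moving down, only as the planning effect and a descriptive relevance benchmark. Report upward and downward movers side by side.

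The cost is one table cell and one sentence, with no added data or patient burden. The rule becomes stricter than the gross reading. The article gives no standard deviation for the score change, so the power of the score test at N=150 cannot be worked out from it. The paired test deals with chance only; the lack of a control group, which the article acknowledges, remains.
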